## Abstract

**Background:**

The first months after birth can be challenging for parents, leading to parental distress and decreased well-being. Parents with high levels of distress are found to respond less adequately and sensitively to their infant, which in turn affects infant well-being and health. The goal of this study is to examine the effectiveness of a psycho-educational intervention to prevent postpartum parental distress and enhance the quality of caregiving and infant well-being. In contrast to other interventions, this intervention will be (1) offered already before birth, (2) offered to all parents-to-be, regardless of their risk of postpartum distress, and (3) include fathers. The proposed study examines the effectiveness of this intervention on (1) parenting distress, (2) quality of caregiving, and (3) the infant’s well-being.

**Methods/design:**

In this randomized controlled trial, 128 pregnant women and their partners will be recruited through midwifery practices and general media. Women with a complicated pregnancy, current psychopathology, insufficient Dutch language proficiency and without Internet access will be excluded. Parents will be randomized to either the intervention or a waitlist control group. The intervention consists of a booklet and video (offered prenatally), a home visit at 34–36 weeks of pregnancy and a telephone call 4 weeks after birth. Information and practical tools are provided on (1) sensitive responding and making contact with the baby, (2) crying, (3) feeding, and (4) sleeping. Assessments will take place at baseline (26–34 weeks of pregnancy), during the home visit (34–36 weeks of pregnancy), and 2, 6, and 10 weeks after birth. The control group will be offered the intervention after the end of the study. The primary outcome is maternal parenting stress. Secondary outcomes are: paternal parenting stress, parental well-being, quality of caregiving, and infant well-being and health.

**Discussion:**

The goal of this study is to test the effects of a psycho-educational prenatal parenting intervention to prevent postpartum parental distress and to enhance well-being in both parents and infants. When the intervention appears effective it can be implemented broadly because of its low costs. It will make support available for a large number of parents and their children.

**Trial registration:**

Netherlands National Trial Register, ID: NTR6065. Registered on 15 September 2016.

**Electronic supplementary material:**

The online version of this article (10.1186/s13063-017-2348-y) contains supplementary material, which is available to authorized users.

## Background

Having a baby is an intense experience that turns the world of new parents upside down. While this life event often brings joy and happiness, the first months can also be challenging for parents (van Scheppingen, Denissen, Chung, Tambs, and Bleidorn, in press [61]). Parents have to develop a range of new skills in taking care for their infant, which requires extra effort and energy, while at the same time they have to deal with a significant lack of sleep. It is not surprising, therefore, that roughly 14% of mothers and 10% of fathers experience moderate or severe levels of postpartum distress [43], mainly consisting of depressive symptoms (e.g., [41]). This study examines the effectiveness of a psycho-educational intervention to prevent postpartum parental distress and enhance infant well-being.

### Parental distress and sensitive responding to the infant’s needs

Parental distress (including, but not limited to, stress related to the parental role) has been related to decreased quality of caregiving. Both maternal [11, 24] as well as paternal depression [46] have been associated with a range of negative outcomes for the child’s emotional, cognitive and behavioral development [21]. The supposed mechanism underlying this link is that depressed parents are less able to respond sensitively to their infant [24, 37]. Sensitivity refers to the extent to which caregivers timeously and appropriately respond to the infant’s needs and signals [2]. Caregiver sensitivity has been identified as one of the most robust predictors of the development of a secure attachment bond between parent and child [3, 20, 30, 55]. Moreover, sensitivity has also been associated with increased social competence, resilience, regulatory capacities, and lower stress levels later in life [23, 25, 50, 52].

Other important characteristics of caregiving behavior are the type of feeding and the infant sleeping location that parents have arranged. Current Dutch guidelines advise parents to exclusively breastfeed for 6 months, and to share their room with the infant for 6 months (infant sleeping in its own crib in the parents’ room, but not in the parental bed) [56, 57]. The World Health Organization (WHO) also recommends exclusive breastfeeding until the infant is 6 months of age [63]. Breastfeeding has been related to important health benefits for the child, including protection against of infections, overweight, and diabetes [28, 62]. Moreover, breastfeeding has been related to increased cognitive development [29]. Next to breastfeeding, there is international agreement on the benefits of room-sharing during the first 6 months of the infant’s life. Room-sharing protects from sudden infant death syndrome (SIDS; [47]). Also, being close to the infant facilitates the process of breastfeeding at night [4, 5]. There are indications that the proximity of the parent functions as a buffer against the infant’s distress [8, 58]. Despite these recommendations, it has been demonstrated that both breastfeeding and room-sharing are frequently discontinued in the first 2 months of the infant’s life [56, 57].

### Interventions to reduce parental distress

There are a number of interventions available that have been proven effective in reducing parental distress ([3, 26, 33, 35, 60]). These interventions mostly start during the postpartum period and are tailored at families from high-risk populations, such as families with low socioeconomic status (SES), parents of an infant born prematurely, foster parents, and parents from children at risk for developing autism spectrum disorder. Moreover, these previous interventions mostly focused on only the mother. This is remarkable because research has shown that the father can play an important role; for example, in supporting the mother with breastfeeding and prolonging the breastfeeding period [38, 44]. Also, intervention studies aimed at treating maternal depression showed that inclusion of the father in treatment led to greater successes of the treatment [54]. Paternal support might protect against maternal stress and the development of postpartum depression, and mitigate the negative effects of depression on the mother-infant interaction [60]. Furthermore, it has also been found that fathers tend to decrease their involvement in childcare when they suffer from psychological adjustment difficulties around the transition to parenthood [31]. Thus, previous research has pointed to the importance of including fathers in the intervention as this might have positive effects on the well-being of both parents as well as on the quality of their caregiving.

To our knowledge, there is only one intervention to date that focused on parents from both low- and high-risk groups. This intervention consists of psycho-education about infant sleep and crying patterns, in combination with a telephone consult and a parent group, and showed positive results in a randomized controlled trial [27]. However, the intervention did not include information on sensitivity or feeding, and it was offered postpartum. Furthermore, as only data of the primary caregiver was collected, almost only data from the mother was available as a result.

### The current study

We developed an intervention which can be offered during pregnancy, to both mothers and fathers, regardless of their risk of postpartum distress. The intervention consists of psycho-education (booklet and video) as well as a prenatal home visit and a postpartum telephone call.

We expect that the proposed intervention will reduce maternal parenting stress. Furthermore, we expect that the intervention will reduce paternal parenting stress and parental distress in general. Moreover, we expect that parental well-being will be enhanced. By psycho-educating parents during pregnancy, we expect parents to experience more self-efficacy and satisfaction in fulfilling their roles. In this way, parents should be better able to provide high-quality caregiving (including breastfeeding and co-sleeping), leading to enhanced infant well-being (less problems with sleeping, crying and feeding, and better well-being and health) (Fig. 1).

**Fig. 1 Fig1:**
[figure not shown]
Primary and secondary study outcomes (jpeg)

### Objectives

The primary objective of this study is to determine the postpartum effect of the intervention on maternal parenting stress. Secondary outcomes are: paternal parenting stress, parental distress in general (anxiety and depression) and parental well-being (satisfaction with the parental role, and self-efficacy in caring for the infant); quality of caregiving (bonding, breastfeeding, and co-sleeping); and infant well-being and health (crying, feeding, sleeping, well-being, and health).

## Methods/design

### Trial design

The study is a randomized controlled trial with two parallel groups: an intervention and a waitlist control group. The waitlist group will receive the intervention after the last assessment (10 weeks after the birth of their infant, see Fig. 2). Please refer to Additional file 1 for the Standard Protocol Items: Recommendations for Interventional Trials (SPIRIT) checklist.

**Fig. 2 Fig2:**
[figure not shown]
Standard Protocol Items: Recommendations for Interventional Trials (SPIRIT) Figure with trial design and outcome assessments. After screening for eligibility, participants are asked to sign an informed consent form and to complete the baseline questionnaire. Then, participants are randomized in either the intervention or the control group. The intervention starts with a home visit (at t1) and a postnatal telephone call (4 weeks after birth). Measurements take place at 26–34 weeks of pregnancy (baseline; t0); 34–36 weeks of pregnancy (t1); 2 weeks after birth (t2; delivery characteristics); 6 weeks after birth (t3); and 10 weeks after birth (t4)

**Fig. 3 Fig3:**
[figure not shown]
Consolidated Standards of Reporting Trials (CONSORT) flow diagram. After screening for eligibility, participants are randomized in either the intervention or the control group. Follow-up measurements take place at 34–36 weeks of pregnancy (t1); 2 weeks after birth (t2; delivery characteristics); 6 weeks after birth (t3); and 10 weeks after birth (t4)

### Study setting and recruitment

Women will be recruited either through midwifery practices or general media (newspaper ads and Internet banners). The midwives will give the parents-to-be a flyer, referring to the study’s website. Alternatively, parents can contact us directly by responding to online advertisements in which a link to the website is provided. On the website, a registration form can be filled out. Upon registering, parents will receive the digital information brochure of the study and an informed consent form. Following the Declaration of Helsinki, it will be clearly indicated on the informed consent form that study participation is entirely voluntary and that participants can withdraw from participation at any time without any negative consequences for them or their child. If parents decide to take part in the study, they will be asked to return the informed consent form. Interested parents who are not eligible for inclusion will receive a message explaining the reason(s) for their exclusion.

### Inclusion and exclusion criteria

Pregnant women will be included in the study when they are before the 34th week of pregnancy and do not have severe medical conditions due to pregnancy (i.e., gestational diabetes or pre-eclampsia). Furthermore, women need sufficient Dutch language proficiency to understand the information offered to them during the intervention (through a booklet and a video). Also, access to the Internet is required to be able to complete the online questionnaires. Women with current psychopathology (defined as current treatment for psychopathology or treatment in the 6 months before inclusion) will be excluded. The partners of the pregnant women will also be asked to participate. However, women without a partner, or women with a partner who does not want to participate, can also enter the study.

### Sample size calculation

We expect an effect size of 0.50 (Cohen’s *d*). This is based on the work of Hiscock et al. [27]. Their intervention, aimed at preventing infant sleep and crying problems, showed an odds ratio of 0.57 (converted into a Cohen’s *d* of 0.48) on symptoms of maternal depression in favor of the intervention group. Using a power of 80%, an alpha of 0.05, we need to include 64 participants in both conditions, 128 in total, to answer our primary research question.

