### Randomization

An independent researcher will generate random number sequences using random allocation software with a 1:1 ratio. We will use random sequence blocks (blocks between 6 and 8), stratified by birth order (first child/ no first child) and paternal participation (yes/no). An independent researcher will allocate each consenting participant to either the control or the intervention group. Given the nature and design of the study, blinding after randomization is not possible. Participants will receive the outcome of randomization by e-mail. Please refer to Fig. 3 for an overview of participant's flow through the study.

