### Statistical analysis

The study will be conducted in adherence to the Consolidated Standards of Reporting Trials (CONSORT) Statement. We will perform intention-to-treat analysis, in which all patients who are randomized will be analyzed (independent of treatment or study completion), as well as completers-only analyses. Completers are defined as participants who completed all measurements. Baseline data will be explored to see if there are differences between the group that remains in the study and the group that drops out.

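### The sample size is justified by a wrong conversion: an odds ratio of 0.57 corresponds to d of about 0.31, not 0.48, and at 0.31 the planned 128 women give about 41% power, not 80%

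*Protocol article*

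**What the plan says.** The section Sample size calculation of the protocol article sets the expected effect at a Cohen's d of 0.50 and attributes it to one earlier trial of a related intervention. That trial is reported to have shown "an odds ratio of 0.57 (converted into a Cohen’s *d* of 0.48) on symptoms of maternal depression", favouring the intervention. The number follows directly: "Using a power of 80%, an alpha of 0.05, we need to include 64 participants in both conditions, 128 in total". The section names no conversion formula, gives no event rates from the earlier trial, and offers no other basis for 0.50, such as pilot data or a minimally important difference.

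Three other places bear on the point. The section Primary outcome under Assessments and outcomes defines the primary outcome as maternal parenting stress, a summed score. The section Randomization allocates "using random allocation software with a 1:1 ratio". The section Statistical analysis plans to compare baseline data between "the group that remains in the study and the group that drops out".

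**The concern.** The input (odds ratio 0.57) and the output (d = 0.48) are both printed, so the conversion can be checked without the cited source. A d of 0.48 looks too large for an odds ratio of 0.57. If the true equivalent is clearly smaller, the evidence cited does not support d = 0.50, and the 80% power is not a property of this trial for the effect used to justify it. The trial could then miss an effect of the cited size more often than it detects it, and a non-significant result could be taken as evidence against the intervention.

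Two lesser points push the same way. The 0.48 is rounded up to 0.50, and the calculation shows no allowance for women without outcome data. Separately, the odds ratio concerns depressive symptoms, whereas the primary outcome is parenting stress.

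**Working it through.** **Inputs, all from Sample size calculation unless noted.** Odds ratio 0.57; stated d 0.48; planning d 0.50; power 80%; alpha 0.05, sidedness not stated; 64 per arm; 1:1 allocation (Randomization).

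**1. Reproduce the plan's number.** A two-sample t-test (noncentral t), two-sided 0.05, d = 0.50 and 80% power needs 63.8, so 64 per arm, with power 80.1%. A one-sided 0.05 test needs only 51 per arm, so the plan's figure is two-sided. The step from d to n is right.

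**2. Convert the odds ratio.** ln(0.57) = −0.562.

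- Logistic: d = |ln OR| × √3/π = 0.562 × 0.551 = 0.31.
- Cox: d = |ln OR| / 1.65 = 0.562 / 1.65 = 0.34.
- Probit: d = z(p₀) − z(p₁), where p₀ is the control prevalence and p₁ follows from p₀ and the odds ratio. The article gives no prevalence, so a range is shown:

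| Control prevalence (assumed) | 5% | 10% | 20% | 30% | 50% |
|---|---|---|---|---|---|
| d | 0.25 | 0.28 | 0.31 | 0.33 | 0.35 |

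The maximum over all prevalences is 0.352. The unscaled |ln OR| is 0.56, which is not 0.48 either.

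**3. Work backwards from 0.48.** Logistic: OR = exp(−0.48 × π/√3) = 0.42. Cox: OR = exp(−0.48 × 1.65) = 0.45. Neither is 0.57.

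**4. Power with 64 per arm, and number needed** (two-sided 0.05, t-test):

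| d | Source | Power at 64 per arm | Per arm for 80% |
|---|---|---|---|
| 0.50 | planning value | 80% | 64 |
| 0.48 | as printed | 77% | 70 |
| 0.34 | OR 0.57, Cox | 48% | 137 |
| 0.31 | OR 0.57, logistic | 41% | 165 |

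The rounding from 0.48 to 0.50 alone saves 6 women per arm. At the largest probit value, power is still only about 51%.

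**5. Missing outcome data (illustration).** The article gives no dropout rate, so 10% and 20% are assumptions, with analysis of observed women only. That leaves 64 × 0.9 = 57.6 or 64 × 0.8 = 51.2 per arm. Power is then 76% or 71% at d = 0.50, and 38% or 34% at d = 0.31.

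**The case against.** The strongest reply is that 41% is the power of an unadjusted comparison at one time point, whereas the section Primary outcome under Statistical analysis plans a mixed multilevel model, with stress measured at baseline, once more in pregnancy and twice after birth. This is fair, and 41% should be labelled as the power of the simple comparison that reproduces the plan's number. But the sample-size paragraph takes no credit for the model, and credit does not close the gap. With 64 per arm, d = 0.31 and baseline adjustment (which the section does not expressly state), dividing d by √(1 − r²) for an assumed baseline–outcome correlation r gives:

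- r = 0.3: effective d 0.325, power 45%.
- r = 0.5: effective d 0.358, power 52%.
- r = 0.7: effective d 0.434, power 68%.
- r = 0.5 with the mean of two follow-ups correlated 0.7: residual variance (1 + 0.7)/2 − 0.5² = 0.60, effective d 0.31/√0.60 = 0.40, power 61%.

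The prenatal items ask about expectations of parenthood, so r may well be low. Including fathers may add something, but the gain is not quantified and the primary objective concerns mothers.

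A second reply is that 64 per arm is correct for d = 0.50. That stands; the fault lies in the reason given for 0.50.

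A third is that some other conversion may have been used. Routes through a correlation come nearer: an approximate tetrachoric correlation turned into d gives 0.45, and Yule's Q turned into d gives 0.57. They do not suit a randomised two-arm factor, and neither yields 0.48.

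The lesser points carry less weight. An article may leave a dropout allowance to the full protocol, and the rates above are assumed. The article says openly that the odds ratio is for depressive symptoms. If that is a poor proxy for parenting stress, 0.31 is no surer a forecast than 0.50, but then the cited trial supports neither. How a null result would be read is a matter of judgement; the article does plan effect sizes and, under its secondary-outcomes heading, 95% confidence intervals.

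**Conclusion.** The concern holds. An odds ratio of 0.57 corresponds to d of about 0.31 (0.25 to 0.35 across the usual methods and control prevalences of 5% to 50%), not 0.48, and this conversion is the only stated basis for d = 0.50. For the effect cited, 128 women with outcome data give about 41% power (48% under the Cox conversion) in a two-sided t-test at 0.05. Under the correlations assumed above, credit for the planned model brings this to roughly 45% to 68%, still short of 80%. The conclusion does not depend on the choice of standard conversion, on any event rate, or on the points about dropout and the proxy outcome. The 80% remains correct for a true d of 0.50.

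**What to change.** Rewrite the sample-size paragraph so that it:

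- gives the conversion as d = 0.31, names the formula, and notes the range of 0.25 to 0.35 by method;
- states that d = 0.50 is the sponsor's own target and is not derived from the cited odds ratio, which concerns depressive symptoms;
- states that 128 women with outcome data give 80% power at d = 0.50 and about 41% at d = 0.31 (two-sided 0.05, t-test), with the lower figures under an assumed 10% to 20% of missing outcomes (76% to 71%, and 38% to 34%);
- adds that a non-significant result will not be taken to exclude an effect of the cited size, and that the confidence interval will be interpreted.

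The cost is one reworded paragraph and a less favourable power figure. The correction requires no increase in enrolment and no change to the endpoint or the analysis. The section Trial status reports recruitment as ongoing, with 59 participants so far, so it can be made before results are known.

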### Randomization

An independent researcher will generate random number sequences using random allocation software with a 1:1 ratio. We will use random sequence blocks (blocks between 6 and 8), stratified by birth order (first child/ no first child) and paternal participation (yes/no). An independent researcher will allocate each consenting participant to either the control or the intervention group. Given the nature and design of the study, blinding after randomization is not possible. Participants will receive the outcome of randomization by e-mail. Please refer to Fig. 3 for an overview of participant's flow through the study.

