#### Baseline variables

At baseline (t0), we assess the demographic characteristics of the parents (date of birth; marital status, income, educational level, and working hours).

Furthermore, to control for possible insecure attachment styles of the parents (which can have an impact on their caregiving quality (e.g., [22]), we will measure attachment styles of the parents using the short form of the Experiences in Close Relationships Questionnaire (ECR-short form; [15, 34]^1^). The 12 items of this instrument are derived from the avoidance and anxious attachment subscales of the ECR-R (six items of each subscale; [10]). Response options vary from 1 (strongly disagree) to 7 (strongly agree). The avoidance subscale measures the need to stay independent from others and to avoid intimacy ([34], see also [7]). The anxiety subscale is concerned with the degree to which the subject worries about rejection and abandonment ([7, 34]). Following recoding of items 15, 25, 27, 29, and 31; for each subscale (anxiety and avoidance) an average score of between 1 and 7 can be computed. Higher scores reflect more attachment anxiety and avoidance. The ECR-short form showed good psychometric properties in different samples: Lafontaine et al. [34] reported Cronbach’s alpha’s of .78 to .87 for the anxiety subscale and .74 to .83 for the avoidance subscale.

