#### Primary outcome

We will compare the parenting stress scores between the two groups using a mixed multilevel model. This way, we can account for the nested structure of the data (mothers and fathers that belong to the same couple). Including both mothers and fathers in one analysis, will positively affect the power of the analyses. Furthermore, the analysis is also robust for missing data (Tabachnik and Fidell, [53]) and unequal sample sizes (more participating mothers than fathers). We will test interaction terms between parental sex (mother versus father) and intervention group (intervention versus control), to test whether the (possible) effect of the intervention is the same for both mothers and fathers. We will also calculate the between-group effect sizes at 6 (t3) and 10 weeks postpartum (t4). We will calculate Cohen’s *d* by subtracting the two mean scores and dividing them by the pooled standard deviations. A Cohen’s *d* of 0.2 can be assumed small, 0.5 to be moderate, and 0.8 to be large [13].

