#### Secondary outcomes

We will repeat the mixed multilevel models, and the calculation of Cohens’ *d*, for all outcomes of parental well-being. Next, to determine the effect of the intervention on the quality of caregiving after birth, we will add higher-quality caregiving as a secondary outcome variable to the model. Furthermore, to test whether prenatal well-being of the parents influences postpartum caregiving quality, we will use parental well-being (measured at 26 and 34 weeks of pregnancy) as a predictor of higher-quality caregiving. Finally, we will determine the effect of prenatal parental well-being on infant outcomes postpartum (mediated by higher-quality caregiving). For each of the outcomes we will calculate the between-group effect size at t3 and t4 and their 95% confidence interval. Gender will be added as an interaction term to the model, to see if there are differences between mothers and fathers.

Demographic data, attachment style of the parents and data related to the delivery and birth (birth weight, Apgar score, spontaneous delivery, caesarean section, birth complications) will be used as control variables in the model.

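### The two factors used to stratify randomisation are absent from the described models, so reported standard errors will be too large if those factors are prognostic

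*Protocol article*

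**What the plan says.** In the protocol article, Randomization describes 1:1 allocation in blocks of 6 to 8, "stratified by birth order (first child/ no first child) and paternal participation (yes/no").

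Under Statistical analysis, Primary outcome, the model is introduced thus: "We will compare the parenting stress scores between the two groups using a mixed multilevel model". The section then mentions the nesting of parents in couples and an interaction of parental sex with group. It names no covariates and no stratification term.

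Under Statistical analysis, Secondary outcomes, the covariates are named: "Demographic data, attachment style of the parents and data related to the delivery and birth" (birth weight, Apgar score, type of delivery, complications) "will be used as control variables in the model". Baseline variables itemises the demographic data as "date of birth; marital status, income, educational level, and working hours". Birth order and paternal participation are in neither list.

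Inclusion and exclusion criteria admits women without a partner and women whose partner declines to take part.

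**The concern.** Stratified blocks force the arms to be nearly equal within each combination of birth order and paternal participation. Differences between strata therefore contribute almost nothing to the random error of the treatment comparison. A model that leaves the strata out still counts those differences as residual variance. Its standard error then describes a trial without stratification and overstates the uncertainty of this one. The balance is bought by the design but not credited in the analysis.

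The trial is sized at 80% power, and the primary-outcome section itself cites power as a reason for pooling mothers and fathers. The covariate list includes delivery data collected after randomisation but omits the two factors fixed before it.

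A second, separate matter concerns the interaction. Every father in the data belongs to a participating couple, while mothers come from both kinds. The mother-father contrast therefore compares two differently composed sets of families.

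**Working it through.** **Inputs.** From Sample size calculation: d = 0.50, 80% power, alpha 0.05, 64 per arm. The standard deviation is 1 on the standardised scale, and two-sided testing is assumed because it reproduces the sample size. The share of outcome variance explained by the two factors (R²) is not given. It is an assumption here, varied from 0 to 0.20, and should be read as the share beyond what the other covariates explain.

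**The plan's own figure.** The normal approximation gives 63 per arm and the t-test 63.8, so 64 per arm reproduces. Power at 64 per arm is 80.7% (normal) or 80.1% (t).

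**Standard error, type I error and power.** With balanced strata:

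- Standard error reported without the factors: sqrt(2/64) = 0.177.
- True standard error, and the one reported with the factors: 0.177 × sqrt(1 − R²).
- Overstatement: 1/sqrt(1 − R²).
- Actual type I error without the factors: 2 × [1 − Φ(1.96/sqrt(1 − R²))].
- Power without the factors: Φ[(0.50/0.177 − 1.96)/sqrt(1 − R²)].
- Power with the factors: Φ[0.50/(0.177 × sqrt(1 − R²)) − 1.96].

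Example at R² = 0.10: sqrt(0.90) = 0.949 and 0.50/0.177 = 2.828. Without the factors, (2.828 − 1.960)/0.949 = 0.915, which gives 82.0%. With them, 2.828/0.949 − 1.960 = 1.021, which gives 84.6%.

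| R² (assumed) | SE overstated by | Type I error without | Power without | Power with |
|---|---|---|---|---|
| 0 | 0% | 5.0% | 80.7% | 80.7% |
| 0.02 | 1.0% | 4.8% | 81.0% | 81.5% |
| 0.05 | 2.6% | 4.4% | 81.4% | 82.7% |
| 0.10 | 5.4% | 3.9% | 82.0% | 84.6% |
| 0.20 | 11.8% | 2.8% | 83.4% | 88.5% |

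**Check by simulation.** The set-up was 128 mothers, four strata, permuted blocks of 6 and 8, and 6,000 runs per scenario. Half were assumed to be having a first child and 80% to have a participating partner.

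- R² = 0.10: type I error 3.8% without the factors and 5.0% with them; power 80.5% and 83.6%. The true standard deviation of the estimate was about 0.169 without and 0.168-0.169 with. The mean reported standard error was 0.1765 without and 0.167 with.
- R² = 0.20: type I error 3.0% and 5.2%; power 82.1% and 88.6%.
- R² = 0: power 80.2% and 80.0%, so including unneeded factors costs almost nothing.

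**The interaction.** Let q be the share of couples with a participating father, ρ the within-couple correlation, and Δ the difference in intervention effect between participating and non-participating couples. In a model with equal variances for the two parents, the expected distortion of the sex-by-group term has size (1 − q)(1 − ρ)Δ. With q = 0.8, ρ = 0.3 and Δ = 0.5 SD (all assumed), this is 0.2 × 0.7 × 0.5 = 0.07 SD. Adding participation as a main effect leaves it unchanged. If Δ = 0 the distortion is zero, however strongly participation itself predicts stress.

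**The case against.** **Silence is not exclusion.** The covariate sentence stands under Secondary outcomes, the primary-outcome section names no covariates, and a condensed article may leave the full model to another document. This carries some weight for the primary model. But the article does commit to a covariate list and itemises it, and the two design factors are not in it.

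**The calculation is simpler than the plan.** It compares 64 with 64 mothers at one time point, whereas the plan is a multilevel model and stress is also measured at baseline. If baseline stress enters the model, or if age, marital status or attachment style overlap with the two factors, the additional R² shrinks. This stands. The upper rows of the table need two yes/no factors to explain a large share of what remains.

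**Prognostic value is not documented.** The article does not say why these factors were chosen. Balancing the number of fathers per arm would be reason enough for one of them. This also stands, and is why R² = 0 is in the table.

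**Stronger readings that the article does not support.** A reader might infer that the estimate itself loses precision; the simulation shows its true spread practically unchanged. A reader might infer that the trial falls below its planned power; power without the factors stays above 80% in every row. A reader might also infer that omitting paternal participation confounds the sex-by-group interaction. Allocation is randomised within participation strata, so a main effect of participation cannot bias that term. Only a different intervention effect by participation could, and a main-effect covariate would not repair it.

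**Conclusion.** The omission is real and worth correcting, but modest. If the two factors are prognostic, the described models report standard errors that are too large. At an assumed additional R² of 0.05-0.10, standard errors are overstated by 2.6-5.4%, type I error is 4.4-3.9% instead of 5%, and about 1-3 power points at d = 0.50 are forgone. The loss is about 5 points at R² = 0.20 and nil at R² = 0. The error is in the conservative direction: there is no bias in the treatment estimate and no inflated false-positive rate.

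The interaction is a separate and conditional matter. It reflects participation as well as parental sex only if the intervention works differently in couples whose father takes part. The article's background stresses the father's supporting role, so this is plausible, but nothing in the article establishes it.

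**What to change.** State that birth order (first child yes/no) and paternal participation (yes/no) enter the primary model and all secondary models as fixed effects. Both are known for every woman at randomisation, so this needs no new data and only a sentence of text. It uses two degrees of freedom among 128 mothers.

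Separately, estimate the sex-by-group interaction, at least as a sensitivity analysis, in couples in which both parents take part. That subset is defined before allocation by a stratification factor, so the comparison within it stays randomised. The cost is a slightly smaller sample of mothers for that one contrast.
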